### Intervention

The training intervention will be conducted over a 12-week period and will consist of exergames using an augmentative virtual reality software (Jintronix, Montreal, QC, Canada) with concurrent a-tDCS. Participants will be required to attend training sessions at Deakin University, Burwood campus, twice per week on non-consecutive days (24 training sessions in total). The exergaming training sessions will be supervised by the attending researcher and will last approximately 30 minutes. Jintronix rehabilitation software, which contains over 100 rehabilitation exergames, along with a three-dimensional motion capture sensor (Kinect®), will be used in this study. The exergames performed by the participants will be pre-selected by the attending researcher and tailored to each participant’s physical needs. The participant’s programmes will include exercises that focus on multiple domains of balance, including bilateral weight transfer, unilateral balance ability, trunk mobility and transitional activities (e.g., standing from a chair). An example balance training programme is illustrated in Fig. 2.

**Fig. 2 Fig2:**
[figure not shown]
Example exergaming programme to improve balance

The exergames will be projected on a wall-mounted flat screen television via a laptop (Fig. 3). The attending researcher will provide standardised verbal feedback to encourage performance throughout each exergaming session. As an embedded feature of each exergame, a completion score will be provided to the participant on-screen, which will represent their performance; for example, a score of five of ten gates achieved in the downhill ski exergame indicates a 50% success rate. The training sessions will be progressed manually by the attending researcher by increasing the difficulty of each exergame. Gaming progression will be based on the participant’s capacity to consistently achieve a score of 80% over two consecutive sessions.

**Fig. 3 Fig3:**
[figure not shown]
Example of anodal transcranial direct current stimulation montage (**a**) and exergaming set-up using Jintronix software (**b**)

A tDCS Stimulator Model 101 (TCT Research Ltd., Kowloon, Hong Kong, China) will be used to deliver real and sham a-tDCS concurrently during exergaming using rubber electrodes (50 mm × 70 mm) placed on the scalp over the M1 to the area which best represents the lower limb (Fig. 3). The optimal lower limb motor representation will be pre-determined by TMS during baseline testing. A midline monopolar anode-electrode montage will be adopted [31], with the cathode placed on the trapezius muscle at the midpoint between the occipital protuberance and acromion process/lateral portion of the scapula spine. For a-tDCS, the intensity will be incrementally increased over the initial 30 seconds to 2 mA and then maintained at that intensity for the duration of the training. Sham a-tDCS will include a 30-second ramp phase to 2 mA to provide sensory stimulation similar to that of real anodal tDCS before returning to baseline. This method of sham stimulation has been used successfully in a-tDCS to blind the participant and attending researcher to the stimulation condition [25, 32]. To ensure double-blinding of the participant and experimenter administering tDCS, blinding codes will be provided to the experimenter prior to the start of the session that activates either the sham or active a-tDCS option.

### Usual care

Participants assigned to the control group will be instructed to continue to receive their usual care from their medical practitioner and community services. In addition, usual care participants will be asked to refrain from partaking in any physical exercise training for the duration of the intervention (i.e., 24 weeks from baseline testing) other than their usual activities of daily living. Upon completion of the follow-up assessment, usual care participants will be offered advice about exercises from the attending researcher.

### Outcome measures

A summary of all outcome measures collected at each time point is shown in Fig. 4 (*also see* Additional file 1: SPIRIT checklist). All outcome measures will be taken at four time points: baseline (week 0), mid-intervention (6 weeks), post-intervention (12 weeks) and follow-up (24 weeks). The mid- and post-intervention testing sessions will occur within 72 hours, but no less than 24 hours, following the preceding training session.

**Fig. 4 Fig4:**
[figure not shown]
Standard Protocol Items: Recommendations for Interventional Trials (SPIRIT 2013) diagram illustrating the schedule of enrolment, post-allocation and close-out for all assessments. *TMS* Transcranial magnetic stimulation, *fNIRS* Functional near-infrared spectroscopy, *UPDRS* Unified Parkinson’s Disease Rating Scale, *mBEST* Mini Balance Evaluation Systems Test, *4SST* Four Square Step Test, *5TSTST* Five Times Sit to Stand Test, *10MWT* 10-Metre Walk Test, *PDQ-39* 39-Item Parkinson’s Disease Questionnaire

### Primary outcome measure

#### Dynamic posturography

The primary outcome will be dynamic balance, which will be measured using the Limits of Stability Test (LOS) delivered through a dynamic computerised posturographic device (NeuroCom SMART Balance Master; Natus Medical, Inc., Pleasanton, CA, USA). The NeuroCom SMART Balance Master consists of two movable force platforms mounted with five strain gauges (100-Hz sampling rate) sensitive to vertical and horizontal shear forces and a visual surround designed to prevent peripheral visual fixation [33]. The force plate and visual surroundings are designed to tilt in an anterior-posterior plane during various testing conditions. A telemonitor mounted on the visual surround provides instructions for each test in addition to visual feedback of the participant’s foot position and movement during the test [33]. The participants will be asked to stand barefoot on the centre of the force platform. Participants will be fitted into a support harness throughout the test to prevent a fall occurring. The two posturographic tests to be performed on the NeuroCom SMART Balance Master are the LOS and the Sensory Organization Test (SOT), which is a secondary outcome measure. The LOS requires each participant to purposefully move their centre of pressure (COP) towards an intended target in the following order: forward, forward right, right, backward right, backward, backward left, left and forward left [27]. Movement velocity (degrees per second), maximal excursion (greatest distance [cm] achieved towards the intended target/maximal distance of target [cm]) and directional control ([the amount of intended movement − amount of extraneous movement)/amount of intended movement] × 100) will be measured. The LOS has shown excellent test-retest reliability for movement velocity (intraclass correlation coefficient [ICC] = 0.825) and sway path length (0.846) [34].

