### Sample size calculation

On the basis of data provided by Shih et al. [31], whose primary outcome was the LOS to assess reaction time and excursion endpoints in people with PD (Cohen’s *d* = 0.74, 77% improvement in reaction time, 89% improvement in endpoint excursion), a sample size calculation using G*Power statistical software estimated a sample size of five participants per group would be sufficient for 85% power (α = 0.05) while using a conservative estimated SD change of ± 5. It is difficult to determine if this is a large-enough sample size to detect change between the real and sham a-tDCS conditions, given the paucity of literature using a testing paradigm of exercise + real a-tDCS vs exercise + sham a-tDCS vs control. However, using the percentage changes between real and sham conditions reported by Kaski et al. [28], we postulate that a sample size of 18 participants will be enough to detect a medium effect size between the real and sham a-tDCS groups (Cohen’s *d* = 0.5) with an estimated SD change of ± 25 for the retropulsion pull test. The LOS and SOT measures were not used by Kaski et al. [28]; therefore, the retropulsion pull test was selected because it contains a balance perturbation similar to that of the SOT. Therefore, to accommodate for a 20% dropout rate, we aim to recruit 8 participants per group (24 participants in total).

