### Statistical analysis

Statistical analyses will be conducted using Stata version 11 statistical software (StataCorp, College Station, TX, USA). A generalised linear mixed model with factors for time (0, 6, 12 and 24 weeks), group (exergaming + sham a-tDCS vs exergaming + real a-tDCS vs control) and group-by-time interaction will be used to determine the effect that different direct current stimulation interventions have on brain excitability and balance. Potential factors such as the participant’s age and time since diagnosis will be used as covariates for analyses within our models. Per-protocol analysis will also be performed by including all participants who are at least 85% compliant with the exercise (as measured by the number of exercise sessions attended). Post hoc analyses using the Bonferroni correction will be applied as appropriate. Pearson’s product-moment correlation coefficient will be used to measure the level of correlation between change scores of the functional tests and brain excitability and activation. Significance will be set at *P* < 0.05.

When possible, we will try to obtain all endpoint measures from any dropouts in the final analysis. For participants who are lost to follow-up, missing data will be handled using the multiple imputation method [63]. Because the multiple imputation method assumes only that data are missing at random [64], we will additionally perform sensitivity analyses to evaluate the potential effect of non-random attrition [65]. Sensitivity analyses will involve testing a range of plausible scenarios in outcomes for participants who were lost during follow-up [66].

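### The primary outcome is a test with three unranked measures over eight directions, and the sizing rests on none of those measures

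*Protocol article*

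**What the plan says.** Protocol article, Dynamic posturography: "The primary outcome will be dynamic balance, which will be measured using the Limits of Stability Test (LOS"). The same section lists what the test delivers: "Movement velocity (degrees per second), maximal excursion (greatest distance [cm] achieved towards the intended target/maximal distance of target [cm]) and directional control", the last defined as a percentage. Participants lean towards eight targets: "forward, forward right, right, backward right, backward, backward left, left and forward left". No measure is singled out, and no average or composite over directions is given. The next section, Static posturography, does name a weighted composite for the secondary Sensory Organization Test (SOT).

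Outcome measures: "All outcome measures will be taken at four time points: baseline (week 0), mid-intervention (6 weeks), post-intervention (12 weeks) and follow-up (24 weeks"). No visit is formally labelled primary.

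Statistical analysis fits time, three-level group and their interaction, sets significance at P < 0.05, and adds: "Post hoc analyses using the Bonferroni correction will be applied as appropriate". The Discussion states two hypotheses: (1) the exergaming groups improve compared with controls, and (2) real stimulation adds to this.

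Sample size calculation starts from a cited study "whose primary outcome was the LOS to assess reaction time and excursion endpoints in people with PD". It then bases real versus sham on a different cited study's retropulsion pull test (Cohen's d = 0.5, 18 participants) and arrives at 24 after 20% dropout.

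**The concern.** A primary outcome is meant to fix in advance the one comparison on which the main claim stands or falls. Here three measures share that status, each can be tested at 0.05, and the only multiplicity rule applies to post hoc analyses. If one measure moves and two do not, the protocol does not say whether the primary result is positive.

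The sizing adds an internal mismatch. A reader would expect it to concern the primary variable, but the variables it names are not in the list of LOS measures. The quoted power therefore cannot be read as power for any measure that the trial will report as primary.

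**Working it through.** **1. The plan's own total.** Reading 18 as 6 per group (an assumption; the text does not divide it): 6 / (1 − 0.20) = 7.5, rounded up to 8; 8 × 3 = 24. This reproduces. The 24 thus follows from the pull-test step, not from the LOS step, which gave five per group.

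**2. Sizing variables against listed LOS measures.**

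| Named in Sample size calculation | Listed in Dynamic posturography? |
|---|---|
| LOS reaction time | No |
| LOS endpoint excursion | No; maximal excursion is related but not the same |
| Retropulsion pull test (source of the 18) | No; chosen for its similarity to the SOT, a secondary outcome |

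The d = 0.74 is not attributed to either LOS variable.

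**3. False-positive chance with three measures at 0.05.** If independent: 1 − 0.95³ = 0.143. The documents give no correlation between the measures, so a range is assumed. Simulating three equally correlated test statistics, with any |z| > 1.96 counted:

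| Assumed correlation | At least one false positive |
|---|---|
| 0 | 14% |
| 0.3 | 13.5% |
| 0.7 | 11% |
| 0.9 | 8% |

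As a check on the model as planned, null trials were simulated with 8 per arm, four visits, correlation 0.5 between visits, and one group-by-time F test per measure on 6 and 63 df (3 × (24 − 3) = 63). At least one of the three interactions was significant in 14% (independent measures), 11% (0.7) and 9% (0.9).

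**4. Interaction against a planned contrast.** Inputs: d = 0.5 for real versus sham (Sample size calculation) and 8 per arm. Assumed: correlation ρ = 0.5 between visits, and a real-arm advantage of 0, 0.25, 0.50 and 0.25 SD at weeks 0, 6, 12 and 24, with sham and control equal.

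- Contrast of change to week 12: noncentrality = d / √(4(1 − ρ)/n) = 0.5 / √(4 × 0.5/8) = 0.5/0.5 = 1.0. Two-sided t on 63 df at 0.05: power about 17%.
- Interaction: the squared deviations of the profile from its mean of 0.25 sum to 0.0625 + 0 + 0.0625 + 0 = 0.125. λ = 8 × (2/3) × 0.125 / 0.5 = 1.33. F on 6 and 63 df: power about 10%.
- With ρ = 0.3 the pair is about 13% and 9%; with ρ = 0.7, about 25% and 15%.
- The same contrast at 0.025 (ρ = 0.5): about 10%.

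**The case against.** The strongest reply is that an article condenses the plan and a separate analysis plan may settle the hierarchy. That covers testing detail, and perhaps the direction summary. It does not cover the identity of the primary outcome, which is stated here as three measures, nor the sizing, which is stated here on others. The authors did find room for a composite for the secondary posturography test.

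Second, Methods/design calls the trial exploratory. That stands and lowers the severity, but the protocol still names a primary outcome, 85% power and a 0.05 level.

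Third, strict use of Bonferroni limits the damage. Correcting over nine pair-by-visit comparisons within each measure gives about 9% (measures correlated 0.7) to 12% (independent) in the same simulation, and requiring a significant interaction first gives about 6% to 8%. This is fair, but the protocol states neither rule, and neither corrects across measures.

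Several stronger readings are tempting and are not supported:

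- A reader might multiply three measures, three pairs and three visits into 27 uncorrected tests and infer an error rate of 1 − 0.95²⁷ = 75%. Statistical analysis assigns Bonferroni to post hoc tests, and the 27 tests are not independent: pairs overlap and changes share a baseline. Modelled uncorrected, they give about 51% to 62%, which is still not the written plan.
- A reader might add the eight directions as separate tests. Nothing says they are tested separately.
- A reader might conclude that no time or contrast is indicated at all. Background and Discussion point to the 12-week effect, and the two hypotheses name the contrasts; what is missing is their formal rank.
- A reader might take the interaction as a gatekeeper. The text does not say so.

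**Conclusion.** The point holds in limited form. Three LOS measures share primary status without ranking, a direction summary or a correction across them, and no sizing step uses a listed measure. The resulting chance of a false primary finding is about 8% to 14% instead of 5%, depending on an assumed correlation between measures of 0.9 down to zero.

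A planned contrast has more power than the 6-df interaction, but the gain should not be oversold. A reader who assumes a 1 SD advantage of real over sham would infer a large rescue of power. The protocol gives no such effect; at its own d = 0.5, with correlation 0.5 and 8 per arm, the step is from about 10% to 17%. Naming one variable therefore repairs the interpretation of the primary result, not the size of the trial.

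Given the exploratory label, this should be fixed and is not a fatal flaw.

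**What to change.** Amend the wording before the stimulation codes are broken and before any LOS data are compared by group:

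- Name one LOS variable, its direction summary and week 12 as primary. Maximal excursion averaged over the eight directions is one example, being closest to the endpoint excursion cited in the sizing. The choice is the investigators'.
- Make the other LOS measures, week 6 and week 24 secondary.
- Test pooled exergaming versus usual care, and real versus sham, as planned contrasts from the same mixed model. Either take them in the order in which the Discussion lists them, or split 0.05 by Bonferroni or Holm.
- State in Sample size calculation that it was not based on the primary variable.

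The cost is wording only; recruitment and measurements are unchanged. The downsides should be stated. No primary claim is possible on the other LOS measures. Splitting alpha loses power (about 17% to 10% for real versus sham at 0.025 under the assumptions above). A fixed order allows no formal second test if the first fails. Putting real versus sham first would be the worse order: it reverses the Discussion's numbering and, at d = 0.5, would block the other hypothesis in about 83% of trials (1 − 0.17).

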### Secondary outcome measures

#### Static posturography

The SOT comprises six different sensory conditions in quiet stance and measures the COP path in centimetres. The test begins with condition 1 (eyes open in a quiet stance) and sequentially moves through each condition, which progressively becomes more challenging by either distracting or removing visual and/or proprioceptive feedback. The visual surround and force platform are sway-referenced, which refers to the tilting of the support surface and/or visual surround in response to movement of the participant’s COP. During the sway-referenced conditions, erroneous sensory information is presented to discombobulate the participant while the force platform measures the participant’s ability to compensate by using other senses to maintain balance equilibrium. The following are the six sensory conditions:*Condition 1*: Eyes open and fixed support*Condition 2*: Eyes closed and fixed support*Condition 3*: Eyes open sway-referenced and support sway-referenced*Condition 4*: Eyes open and support sway referenced*Condition 5*: Eyes closed and support sway-referenced*Condition 6*: Eyes open and sway-referenced with support sway-referenced

The composite equilibrium score, presented as a weighted average percentage of the six conditions, will be used to determine overall static balance performance and has shown good reliability (ICC = 0.67) [35]. Additionally, the sensory analysis ratios obtained from specific sensory test condition pairs will be used to determine the level of reliance on different senses to maintain balance equilibrium [36]. The following ratios will be used:Somatosensory ratio ([SOT2/SOT1] × 100) will measure the participant’s reliance on the somatosensory system to maintain balance equilibrium.Visual ratio ([SOT4/SOT1] × 100) will measure the participant’s reliance on the visual system to maintain balance equilibrium.Vestibular ratio ([SOT5/SOT1] × 100) will measure the participant’s reliance on the vestibular system to maintain balance equilibrium.Visual preference ratio ([SOT 3 + 6/SOT 2 + 5] × 100) will measure the participant’s reliance on visual information, even when the information is incorrect, to maintain balance equilibrium.

Participants will have only a single practise trial for each sensory condition to minimise any practise effect between testing protocols. If the participant requires assistance or takes a considerable step away from the force plate, it will be registered as a loss of balance, and an equilibrium score of zero will be indicated.

#### Transcranial magnetic stimulation and electromyography

Single- and paired-pulse TMS of the M1 will be conducted using a BiStim^2^ 200^2^ magnetic stimulator (Magstim Co., Whitland, UK) to measure changes in corticospinal excitability and intracortical inhibition of the tibialis anterior (TA) muscle. The TA was selected as the target muscle because it is primarily involved with postural balance [37]. Prior to TMS, all participants will wear a custom-made nylon cap marked with a 1-cm concentric grid that extends outward from the vertex. A double-cone TMS coil with a wingspan of 110 mm will be positioned directly over the vertex of the head, and the optimal site of stimulation will be determined by initial exploration around the vertex that produces the largest and most consistent motor-evoked potential (MEP) recordings from the TA. Once the optimal site of stimulation has been identified, the resting motor threshold (RMT) will be determined. The RMT is defined as the lowest TMS intensity that produces an average MEP amplitude between 50 and 100 μV in response to five of ten stimuli [38]. Ten single-pulse TMS stimuli will then be delivered at 80%, 100%, 120%, 140% and 160% of RMT each to establish a stimulus-response curve that will be used to measure changes in corticospinal excitability with excellent reliability (ICC = 0.986) [38].

Corticocortical inhibitory circuits are suppressed in people with PD [39], and therefore paired-pulse TMS will be used to determine changes in short-interval/long-interval intracortical inhibition (SICI/LICI). Paired-pulse TMS will be delivered using a conditioning stimulus-test stimulus paradigm separated by a set interstimulus interval (ISI), which has shown excellent reliability (ICC = 0.934) [38]. To measure SICI, the CS will be set at 0.8 RMT, whereas the TS will be set at 1.2 RMT, separated by an ISI of 3 milliseconds [40]. For LICI, both the CS and TS will be set at 1.2 RMT, separated by an ISI of 100 milliseconds [41]. To calculate SICI and LICI, ten conditioned and unconditioned TS at the respective ISIs will be delivered and expressed as a percentage change of the average conditioned to unconditioned TS response. Surface electromyography (sEMG) can detect the level of muscle activity induced from transcranial stimulation and will be recorded using two bipolar Ag-AgCl electrodes 2 cm apart over the muscle belly of the TA and a ground electrode placed over the patella [42]. Prior to applying the electrodes, the participant’s skin will be shaved and swabbed with alcohol. All sEMG signals will be amplified (× 1000) with band-pass filtering between 5 Hz and 500 Hz, sampled at 4000 Hz and collected via a laboratory analog-digital interface (PowerLab 8/30; ADinstruments, Bella Vista, Australia) for later offline analysis.

#### Cognitive function

E-Prime software (Psychology Software Tools, Sharpsburg, PA, USA) [43] will be used to design two fNIRS-compatible computer-based cognitive assessments using a three-block design with a 30-second task period offset with a 30-second rest period. The Stroop colour-word test and the Go/No-Go test will be used to assess executive function, in particular response inhibition, interference control, attention and choice reaction time. In the Stroop colour-word test, participants will be presented with two conditions: incongruent and congruent. The incongruent condition will randomly present two colour words (red and green) written in opposing ink colours (e.g., the word ‘red’ will be written in green ink). For the congruent condition, the word and ink colour are the same (e.g., the word ‘red’ will be written in red ink). Upon presentation of the word, the participant must strike the key indicating the colour of the word presented, and the response time will be recorded in seconds. Cognitive central processing ability will be determined by measuring the difference in response times between the two conditions [29].

The Go/No-Go task is a choice reaction time test that requires participants to either strike or delay striking the left mouse button during two separate conditions (go and no-go). In the ‘go’ condition, the participants will be presented with a random series of letters and will be asked to strike the left mouse button as fast as they can as each letter appears. In the ‘no-go’ condition, a further random series of letters will appear; however, the participant will be asked to delay striking the mouse only when the letter ‘X’ appears. The reaction time for each response during each condition will be recorded in seconds.

